**5.8.2 MANOVA Analyses**

Multivariate analysis of variance (MANOVA) will be used to assess pre and post-test differences across outcome variables. Separate MANOVA analyses will be conducted for primary outcome variables focused on HIV/STI (HIV knowledge, STI knowledge, HIV/STI risk factors, relationship power) and secondary outcome variables focused on mental health (depression, trauma, resilient coping, social support). We will compare differences in participant scores from the pre-test and post-test (after the 6-weekly health meetings) to assess if the intervention influenced any of the primary or secondary outcomes. We will conduct a multivariate analysis of covariance (MANCOVA) to control for the number of weekly health meetings attended. Significant MANCOVA will be followed up with both univariate tests and discriminant function analyses (DFA) to understand significant effects. DFA can be used to identify variates (combinations of dependent variables) and how the dependent variables contribute to the variates. Analyses will be conducted using SPSS 19 software.

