**5.4 Outcome Measures**

The survey will be based on pre-existing scales with reported reliability and validity. The primary outcome is: (1) HIV knowledge. The secondary outcomes are: (2) STI knowledge, (3) condom use, (4) relationship control, (5) depression, (6) resilient coping, and (7) social support.

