**5.4.1 Primary Outcome**

**HIV knowledge** will be assessed using the 18-item Brief HIV Knowledge Questionnaire (Carey & Schroder, 2002).

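### Section 5.4 makes HIV knowledge the only primary outcome, but 5.8.2 tests four primary outcome variables in one MANOVA, and HIV knowledge gets its own test only after a significant MANCOVA

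*Protocol*

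**What the plan says.** Protocol section 5.4 sets the hierarchy: "The primary outcome is: (1) HIV knowledge". It continues: "The secondary outcomes are: (2) STI knowledge, (3) condom use, (4) relationship control, (5) depression, (6) resilient coping, and (7) social support". Section 5.4.1, headed as the primary outcome, contains HIV knowledge alone, which "will be assessed using the 18-item Brief HIV Knowledge Questionnaire".

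Section 5.8.2 groups the outcomes differently: "Separate MANOVA analyses will be conducted for primary outcome variables focused on HIV/STI (HIV knowledge, STI knowledge, HIV/STI risk factors, relationship power"). The second MANOVA covers "secondary outcome variables focused on mental health (depression, trauma, resilient coping, social support"). The stated aim is "to assess if the intervention influenced any of the primary or secondary outcomes". A MANCOVA is then to adjust for the number of weekly meetings attended. Tests of single outcomes appear at one place only: "Significant MANCOVA will be followed up with both univariate tests and discriminant function analyses (DFA) to understand significant effects".

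**The concern.** The two sections give different answers to what a positive primary result is. Under 5.4 it is a change in HIV knowledge. Under 5.8.2 it can be read as a significant multivariate test on four variables, at least two of which 5.4 ranks as secondary.

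The declared primary outcome has no unconditional test of its own. Its univariate test is described only as a step after a significant MANCOVA, and nothing says that this univariate result, rather than the multivariate one, decides the primary question. A report of a significant effect on the primary outcomes, with HIV knowledge flat, would comply with 5.8.2 and contradict 5.4. In some circumstances a real change in HIV knowledge might also fail to reach its own test.

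**Working it through.** **1. The sections side by side**

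| Variable | Section 5.4 | Section 5.8.2 |
|---|---|---|
| HIV knowledge | primary | primary set |
| STI knowledge | secondary | primary set |
| Relationship control/power | secondary | primary set |
| Condom use | secondary | not named |
| HIV/STI risk factors | not named | primary set |
| Depression, resilient coping, social support | secondary | secondary set |
| Trauma | not named | secondary set |

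HIV/STI risk factors appears to stand for condom use, but the protocol never equates the two. The firm contradiction therefore covers STI knowledge and relationship power; for the third added variable the names have to be reconciled first.

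**2. The plan's own figure**

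Section 5.6.1 counts 7 outcomes at 20 participants each and gives a minimum of 160. But 7 × 20 = 140, whereas 8 × 20 = 160, which matches the eight variables of 5.8.2. This is a further sign that the outcome lists were not aligned. The calculations below take 160 as the number of completers.

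**3. Size of the consequences**

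Assumptions, none given in the protocol: n = 160 independent pairs, two-sided 5%, no attendance covariate, any change equal to d = 0.25 SD of the change score, common correlation ρ between change scores of 0, 0.3 or 0.5.

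*Direct paired test on HIV knowledge.* Noncentrality d√n = 0.25 × √160 = 3.16, with 159 df and critical value 1.975. Power is 88%.

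*Four-variable omnibus test*, in paired form (one-sample Hotelling T²). It is referred to F with 4 and 156 df, critical value 2.43, noncentrality λ = n·δ′R⁻¹δ. If a single variable changes, λ = n·d²·r, where r is the diagonal element of R⁻¹: 1.00, 1.203 and 1.60 at ρ = 0, 0.3 and 0.5. Since n·d² = 160 × 0.0625 = 10, λ = 10.0, 12.0 and 16.0.

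| What truly changes, by 0.25 | ρ = 0 | ρ = 0.3 | ρ = 0.5 |
|---|---|---|---|
| One other variable, HIV knowledge flat: omnibus significant | 70% | 79% | 90% |
| HIV knowledge only: omnibus significant | 70% | 79% | 90% |
| HIV knowledge only: direct paired test | 88% | 88% | 88% |
| HIV and STI knowledge: omnibus significant (λ = 20.0, 19.5, 24.0) | 96% | 95% | 98% |

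The first two rows agree because the model treats the four variables alike.

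**4. The two-step route, by simulation (20,000 runs, same assumptions, the omnibus test standing in for the MANCOVA)**

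- One other variable changes: the omnibus test is significant while the HIV knowledge test is not in 65%, 74% and 85% of trials. In these trials the two definitions of the primary result disagree.
- Only HIV knowledge changes: both steps are significant in 70%, 76% and 84%. A significant HIV knowledge test sits behind a non-significant omnibus test in 19%, 12% and 5%.
- Nothing changes: the omnibus test is significant in about 5%.

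**The case against.** Several stronger readings are tempting, and the protocol does not support them.

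- *HIV knowledge is never tested on its own.* It is, conditionally: 5.8.2 provides univariate tests after a significant MANCOVA. What is missing is an unconditional test and a rule giving it priority.
- *The 70% to 90% is a false-positive rate.* It is power to detect a real change in another variable. With no change anywhere the test rejects about 5% of the time. Harm arises only if the omnibus result is presented as the primary result, and the univariate follow-up would show which variable moved. The protocol does not exclude that presentation, but it does not announce it either, so planned outcome switching cannot be inferred.
- *The MANOVA loses power for the primary outcome.* Only if HIV knowledge moves alone and change scores are weakly correlated. The meetings also cover STIs, relationships and communication, so joint change is plausible, and then the omnibus test is the more powerful.

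It can also be said that the model is not the planned procedure: it omits the attendance covariate and treats women as independent, although each peer health worker runs meetings for her own 25 women. That stands; the percentages are illustrative. Finally, details of test, alpha and interval may sit in a statistical analysis plan that is not shown. Such a plan could follow only one of the two sections, and the protocol would still contradict itself.

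**Conclusion.** The point holds as a contradiction in the current text. Sections 5.4 and 5.4.1 fix one primary outcome; 5.8.2 analyses four under that label, with only a conditional test of the declared one and no rule for which result decides. That needs resolving before data are seen, and the conclusion rests on the text, not on the percentages.

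The percentages show that the choice of definition is not a formality. Under the assumptions stated, with HIV knowledge flat and one other variable moving by 0.25 SD, the test labelled primary is significant in 70% to 90% of trials. The missed-change risk is secondary and conditional. If only HIV knowledge moves, the omnibus test gives up 18 points at correlation 0 (88 − 70) and 9 at 0.3 (88 − 79), and nothing at 0.5, where only the requirement to pass both steps still costs about 4 (88 − 84). The comparison reverses, 95% to 98% against 88%, if STI knowledge changes as well.

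**What to change.** In 5.8.2, make the primary analysis the mean within-woman change in the HIV knowledge score from pre-test to post-test, with a 95% CI, tested alone at two-sided 5% and reported whatever the MANOVA or MANCOVA shows. Relabel the four-variable MANOVA as secondary and state that significance there is not a positive primary result. Use the same outcome names in 5.4 and 5.8.2: say whether HIV/STI risk factors means the condom-use items, use one term for relationship control or power, and either list trauma in 5.4 or drop it from 5.8.2.

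Declaring four primary outcomes in 5.4 with a stated multiplicity rule would also remove the contradiction, but it departs from the hierarchy that 5.4 and 5.4.1 already set.

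The cost is a wording change and one simple analysis, with no new data, visits or participants. The small downside is that the other three variables can no longer be claimed as primary.

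### HIV knowledge is the only primary outcome in section 5.4 but one of four in 5.8.2, which plans no test of it outside the follow-up to a significant MANCOVA

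*Protocol*

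**What the plan says.** Section 5.4 of the protocol is explicit: "The primary outcome is: (1) HIV knowledge". The same section gives the secondary outcomes as "2) STI knowledge, (3) condom use, (4) relationship control, (5) depression, (6) resilient coping, and (7) social support". Section 5.4.1 has one entry, HIV knowledge, which "will be assessed using the 18-item Brief HIV Knowledge Questionnaire". Section 5.4.2 places STI knowledge, relationship power and condom use among the secondary measures.

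Section 5.8.2 sets out two separate MANOVAs. The first covers "primary outcome variables focused on HIV/STI (HIV knowledge, STI knowledge, HIV/STI risk factors, relationship power"; the second covers "secondary outcome variables focused on mental health (depression, trauma, resilient coping, social support". The multivariate test comes first: "Multivariate analysis of variance (MANOVA) will be used to assess pre and post-test differences across outcome variables". A MANCOVA with the number of meetings attended as covariate is added, and the single-outcome tests depend on it: "Significant MANCOVA will be followed up with both univariate tests and discriminant function analyses (DFA) to understand significant effects". The purpose of the pre-post comparison is given as "to assess if the intervention influenced any of the primary or secondary outcomes". The protocol states no significance level and does not say which of these tests settles the primary question.

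**The concern.** The two sections cannot both be followed. STI knowledge and relationship power are secondary in 5.4 and primary in 5.8.2. A SAP written from this protocol would have to depart from one of them.

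The planned order of testing adds to this. The outcome declared primary in 5.4 has no test of its own; it is reached only as a follow-up to a multivariate test. That joint test asks whether any combination of four outcomes changed, which is a different question from whether HIV knowledge changed. In an uncontrolled pre-post study (section 5.1), one pre-specified primary test is a main protection against selective reporting. As the text stands, an improvement in STI knowledge or relationship power could be presented as a primary success while HIV knowledge showed nothing.

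**Working it through.** **1. The outcome lists side by side**

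| Outcome | 5.4 to 5.4.2 | 5.8.2 |
|---|---|---|
| HIV knowledge | primary | primary |
| STI knowledge | secondary | primary |
| Relationship control / power | secondary | primary |
| Condom use | secondary | not named |
| HIV/STI risk factors | not named | primary |
| Depression, resilient coping, social support | secondary | secondary |
| Trauma | not named | secondary |

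So there is one primary outcome in 5.4 and four in 5.8.2, and seven outcomes in total in 5.4 against eight in 5.8.2. Condom use is probably what 5.8.2 means by HIV/STI risk factors, but the protocol does not say so.

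**2. What each result of the joint test would mean**

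- Significant: at least one combination of the four outcomes changed. This may or may not involve HIV knowledge.
- Not significant: 5.8.2 plans no univariate test, so HIV knowledge is not tested alone.
- The stated condition is the MANCOVA. No univariate follow-up of the MANOVA is described. Two multivariate tests are therefore planned per family, and neither is named as decisive.

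**3. Possible cost in power (illustration)**

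The protocol has no figure to reproduce here: it gives no alpha, effect size, SD or correlation. Assumptions: n = 160 independent pairs (the minimum named in 5.6.1), two-sided 5%, equal correlation ρ among the four change scores, no covariate, standardised change d = 0.223 in HIV knowledge only.

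- Paired t-test: noncentrality d√n = 0.223 × √160 = 2.82, df 159, critical value 1.975. Power 80%.
- Joint test (one-sample Hotelling T², 4 outcomes): noncentrality λ = n d² × c, with c = (1 + 2ρ) / [(1 − ρ)(1 + 3ρ)], referred to F with 4 and 156 df, critical value 2.43.

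| ρ | c | λ | Joint test, only HIV knowledge changes | Joint test, two outcomes change by 0.223 SD |
|---|---|---|---|---|
| 0 | 1.00 | 7.96 | 59% | 90% |
| 0.3 | 1.20 | 9.57 | 68% | 89% |
| 0.5 | 1.60 | 12.73 | 82% | 95% |

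The λ column belongs to the case where only HIV knowledge changes. At d = 0.25 and ρ = 0 the figures are 88% (paired) and 70% (joint). A claim on HIV knowledge needs both tests to be significant, so its power can never exceed that of the paired test. At d = 0.20, simulation gave 47% for both together at ρ = 0 and 53% at ρ = 0.3, against 71% for the paired test alone.

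**4. False positives after the joint test**

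If one of the four outcomes truly changes, so that the joint test is significant, three unchanged outcomes remain. Each tested at 5% and independent: 1 − 0.95³ = 0.143, about 14%. Simulation with one outcome changing by 0.5 SD gave 14.1% at ρ = 0 and 13.1% at ρ = 0.3.

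For HIV knowledge alone, when it has not changed but another outcome has changed by 0.5 SD, the simulated false-positive rate was 5.2% at ρ = 0 and 4.9% at ρ = 0.3, that is, the nominal 5%.

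**The case against.** The strongest reply is that 5.4 and 5.4.1 do define a primary outcome and its instrument, that the remark about any of the outcomes states an aim and not a rule for success, and that alpha and multiplicity are commonly left to a SAP, which is not shown. Part of this stands. Silence on alpha is not a fault here, and the outcome itself is defined once. But the contradiction lies between two current sections of the protocol, and a SAP could resolve it only by overriding one of them.

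Four stronger readings are tempting and go too far:

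- A reader might infer that HIV knowledge has no error control. It has: a claim needs its own univariate test to be significant, so at a 5% level its false-positive rate cannot exceed 5%. The 14% concerns the other three outcomes.
- A reader might infer that power is always lost. The 59% needs HIV knowledge alone to change and the outcomes to be uncorrelated. The weekly sessions also address STIs, relationships and communication, so change in several outcomes is plausible, and the joint test then has 89% to 95%.
- A reader might add up the two families (1 − 0.95² = 9.75%). That pools the primary set with one that 5.8.2 itself labels secondary; a false positive there is not a false primary success.
- A reader might take the MANOVA as the condition for the univariate tests. The text ties them to the MANCOVA, and the power figures above, which use no covariate, only approximate that test.

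**Conclusion.** The point holds. The protocol names one primary outcome in 5.4 and four in 5.8.2, plans a single-outcome test of HIV knowledge only after a significant MANCOVA, and does not say which test decides. This follows from the text alone and depends on no assumed number. To say that the trial has no success criterion at all would be stronger than the text supports: the primary outcome and its instrument are stated in 5.4, and what is missing is an agreed test of it.

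The size of the consequence is illustrative. Power for the declared primary outcome may fall from 80% to 59% in the least favourable case examined, with a smaller loss at correlation 0.3 and little or none at 0.5 or when several outcomes change. The chance of at least one false positive among the other three outcomes is about 14% once one true effect makes the joint test significant, if they are independent and each is tested at 5%. These figures also ignore the shared group sessions (25 women per peer health worker).

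**What to change.** In 5.8.2, state that the single primary analysis is the within-woman change, pre-test to post-test, in the 18-item HIV knowledge score, tested once at two-sided 5% and not conditional on any MANOVA or MANCOVA.

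Rename the two families HIV/STI outcomes and mental-health outcomes, and state that every outcome other than HIV knowledge is secondary. The MANOVAs, the MANCOVA and the discriminant analysis can stay as secondary analyses.

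Reconcile the outcome lists. Trauma is analysed in 5.8 but absent from 5.4, so either add it to 5.4 with its measure or remove it from 5.8. Say whether condom use in 5.4 and HIV/STI risk factors in 5.8 are the same outcome, and use one name for relationship control and relationship power. Align the count of seven outcome variables in 5.6.1 with the final list.

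The cost is protocol wording only: no extra participants, visits or data. The downside is that secondary outcomes can no longer be reported as primary successes.

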**5. METHODOLOGY**

**5.1 Overall approach**

We will develop and field test a solar-powered tablet technology that synchronizes HIV/STI prevention messages with a participant’s responses in Leogane, Haiti. The tablet will be programmed to analyze the data and to generate a brief video-based counseling message for the peer health worker (PHW) and participant that involves HIV/STI risk reduction strategies.

A pre and post-test N-of-1 trial design will be used. Outcomes (HIV/STI knowledge, HIV/STI risk factors, mental health issues, coping, relationship power) will be measured at baseline and 3 months post-intervention. Participants (n=200) will receive a high intensity HIV/STI educational intervention: a) tablet-based intervention using an HIV/AIDS educational video; b) 6 weekly sessions of women’s health discussions. The control group will include the same group by testing the outcomes at baseline.

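### Protocol 5.8.2 adjusts the pre-post comparison for meetings attended, which is the dose of the intervention, and names that adjusted MANCOVA as the only trigger for the outcome-level tests, including HIV knowledge

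*Protocol*

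**What the plan says.** Section 5.1 of the protocol defines the intervention as "a) tablet-based intervention using an HIV/AIDS educational video; b) 6 weekly sessions of women’s health discussions". It has one group, with its own baseline as comparator: "The control group will include the same group by testing the outcomes at baseline".

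Section 5.8.2 sets out the analysis in this order.

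- An unadjusted test: "Multivariate analysis of variance (MANOVA) will be used to assess pre and post-test differences across outcome variables". Its stated purpose is "to assess if the intervention influenced any of the primary or secondary outcomes".
- An adjusted test: "We will conduct a multivariate analysis of covariance (MANCOVA) to control for the number of weekly health meetings attended".
- The follow-up: "Significant MANCOVA will be followed up with both univariate tests and discriminant function analyses (DFA) to understand significant effects".

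Sections 5.4 and 5.4.1 make HIV knowledge the single primary outcome. Section 5.8.2 gives it no stand-alone test; it sits in a set of four HIV/STI outcomes. The section does not say whether attendance is centred, whether pre and post are handled as repeated measures or as two groups, or which term of the MANCOVA has to be significant.

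**The concern.** A covariate is usually adjusted for because it could distort the comparison. Attendance cannot do that here. Each woman is compared with herself, and the count only comes into being after the pre-test. It records how much of the intervention she took up, and she chose that herself. Research Question 2 asks about change from before to after the programme with other effects held constant, but attendance is the programme and not one of the other effects.

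Adjusting for the dose would matter little as a side analysis. It matters because section 5.8.2 attaches the univariate tests to the adjusted model. The route to a result on HIV knowledge therefore runs through a test whose meaning depends on choices the protocol leaves open, and under one ordinary set of choices that test has almost no power against a real change.

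**Working it through.** **Inputs from the protocol.** Six meetings (5.1), so the count runs from 0 to 6. Four outcomes in each MANOVA set (5.8.2). Recruitment target 200, stated minimum 160 (5.6.1). The 160 is not a power figure: the rule given there, 20 per variable for 7 variables, yields 20 × 7 = 140, while 20 × 8 = 160. It is used below only as a sample size.

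**Assumptions, because the protocol gives no values.** Two-sided level 0.05; mean change of 0.3 SD of the change score on each of the four outcomes; correlation 0.3 between change scores; attendance Binomial(6, p) with mean 3.6, 4.8 or 5.4.

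**Step 1: what the time effect estimates.** In a repeated-measures model with attendance A as covariate, the time effect is the intercept a in

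change = a + b × A + error.

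With A as the raw count, a is the expected change for a woman who attended no meetings. With A centred at its mean, a is the mean change.

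**Step 2: loss of precision at zero.** Relative to the unadjusted mean change, the standard error of the raw-count intercept is larger by about sqrt(1 + mean²/variance) of attendance:

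- mean 3.6, variance 1.44: sqrt(1 + 12.96/1.44) = sqrt(10) = 3.2
- mean 4.8, variance 0.96: sqrt(1 + 23.04/0.96) = sqrt(25) = 5.0
- mean 5.4, variance 0.54: sqrt(1 + 29.16/0.54) = sqrt(55) = 7.4

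**Step 3: power in closed form when change is unrelated to attendance, n = 160.** The noncentrality of the unadjusted Hotelling test is 160 × 0.3² × 4 / (1 + 3 × 0.3) = 57.6/1.9 = 30.3, which gives power above 0.99. Dividing by 10, 25 and 55 gives 3.0, 1.2 and 0.55, with power 0.24, 0.12 and 0.08.

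**Step 4: simulation, 2,000 trials per setting, n = 160.** Each cell gives power at mean attendance 3.6 / 4.8 / 5.4.

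| Test used as the gate | Change wholly proportional to attendance | Change unrelated to attendance |
|---|---|---|
| Unadjusted pre-post | 0.998 / 0.994 / 0.998 | 0.998 / 0.998 / 0.996 |
| Time effect, raw count, repeated measures | 0.054 / 0.043 / 0.050 | 0.248 / 0.123 / 0.071 |
| Time effect, mean-centred count, repeated measures | 0.998 / 0.994 / 0.998 | 0.998 / 0.998 / 0.996 |
| Time effect, pre and post as two groups, same count on both rows | 0.660 / 0.654 / 0.654 | 0.680 / 0.650 / 0.670 |
| Time effect, two groups, count set to 0 at pre-test | 0.092 / 0.098 / 0.124 | 0.196 / 0.142 / 0.128 |
| Attendance slope | 0.262 / 0.114 / 0.076 | 0.057 / 0.046 / 0.050 |

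The raw-count row agrees with step 3. If half the change is dose-related, the raw-count time test has power 0.06 to 0.08. With 200 women it has 0.05 to 0.06 (all dose-related) and 0.09 to 0.30 (unrelated). Raising the change to 0.5 SD, all dose-related, leaves it at about 0.05, because the true change at zero meetings is then nil.

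**Step 5: other assumptions.** A second simulation with 160 women, 4 outcomes, a change of about 0.30 SD in HIV knowledge and mean attendance 5.0 or 3.9 gave 86 to 89% unadjusted. The raw-count time test gave 5% for a proportional effect, and 11% or 22% for a change unrelated to attendance. The unadjusted figure depends on the assumptions; the collapse under raw-count coding appears in both.

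**Step 6: reading across.** The same-count row loses power because treating pre and post as two groups ignores the pairing; its contrast is still the mean change. The slope row tests whether change varies with attendance, which is a different question from whether there was change.

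**The case against.** The strongest reply is that the zero-meetings result follows from one model and not from the protocol's words. It needs a raw count, a within-woman model and the time effect as the gate, and section 5.8.2 states none of these. A statistical analysis plan could centre the count, and power would then equal that of the unadjusted test. This stands. A reader might infer that the MANCOVA must estimate change at zero attendance, or that it cannot recover the programme's average change under any coding. The documents support neither: centred and same-count coding both target mean change.

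The second reply is that the unadjusted MANOVA is already planned and comes first. This also stands. A reader might infer that a working programme would be declared ineffective, but that would mean setting aside a planned test which has 86% power or more under the assumptions above.

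Third, 5.8.2 does not say that a significant MANOVA goes without follow-up. True, but the MANCOVA is the only trigger it names.

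Fourth, the 5% is a worst case. Zero meetings need not mean zero intervention, since section 5.3.1 offers an optional video after the survey. That is fair, and is why the range for a change unrelated to attendance is given beside it.

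What the replies do not provide is a reason for the adjustment. In the codings examined it either weakens the gate, changes the question, or leaves the estimated change as it was. This is also more than missing detail: a later plan that follows 5.8.2 would still control for the dose and still gate on the adjusted model.

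**Conclusion.** The point holds in conditional form. Section 5.8.2 adjusts for a self-selected, post-baseline measure of dose and makes that adjusted model the only named trigger for the outcome-level tests, HIV knowledge among them. Under raw-count repeated-measures coding with the time effect as gate, power at 160 women falls to about 5% (change wholly proportional to attendance) or about 7 to 25% (unrelated; up to 30% with 200 women), against 86% or more unadjusted. Under centred or same-count coding the target is still the mean change and nothing is gained. If the attendance slope is the gate, it does not test the pre-post change at all.

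The figures rest on assumed attendance, effect size and correlation, none of which the protocol gives. The exposure is limited to the outcome-level follow-up, because the unadjusted MANOVA remains. This should be fixed, but it does not invalidate the planned overall comparison.

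**What to change.** Reword the two sentences in 5.8.2 on the MANCOVA and its follow-up.

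- Tie the univariate tests, the discriminant analysis and the HIV-knowledge test to the unadjusted within-woman pre-post comparison already planned, in all women regardless of how many meetings they attended.
- Report attendance separately as an exploratory dose-response analysis: change regressed on mean-centred attendance, labelled non-causal because attendance is self-selected.

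No new data or visits are needed. The unadjusted comparison still measures change in a single group with its own baseline as control; removing the covariate does not alter that limit.

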Surveys will be implemented in a private room within NEGES, an agency which participants are familiar with and many already attain services. Multiple strategies will be employed to protect confidentiality of participants. The PHW will be trained and 1) a significant part of the training will be regarding confidentiality and ethics and 2) the PHW will sign confidentiality agreements to protect confidentially of participants. No names or other identifying information will be collected on surveys or informed consent sheets, and informed consent sheets and surveys will be kept at a locked filing cabinet in NEGES. The surveys will have an ID number so pre and post-test scores can be compared. A sheet with the ID number and participants first name and last initial will be kept in a locked filing cabinet at NEGES; PHW will only have access to this sheet during data collection. Participants will also have an option to keep an informed consent sheet, which will be evidence of survey participation, or to have access to it at NEGES. Signatures will not be required for the informed consent; to enhance confidentiality participants can sign with an X.

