**5.6** **Participant Recruitment**

**5.6.1 Sample Size Justification**

This study will aim to recruit 200 participants. There are 7 outcome variables, and a minimum sample size of 20 participants per variable is recommended for MANOVA (Field, 2009). Due to the possibility of attrition in this population we will aim to recruit 200 participants although 160 would be the minimum sample size required to detect a significant effect.

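### Discriminant function analysis in Section 5.8.2 would treat the same women's pre-test and post-test records as two independent groups, so its tests and weights do not describe within-woman change (minor)

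*Protocol*

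**What the plan says.** Section 5.1 describes a single group with baseline as its own comparator: "The control group will include the same group by testing the outcomes at baseline". Section 5.3.1, activity (4), links the two measurements: "The surveys will have an ID number so pre and post-test scores can be compared".

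Section 5.8.2 tests time: "Multivariate analysis of variance (MANOVA) will be used to assess pre and post-test differences across outcome variables". One of the two outcome sets holds four outcomes, given as "primary outcome variables focused on HIV/STI (HIV knowledge, STI knowledge, HIV/STI risk factors, relationship power". A MANCOVA then adjusts for the number of weekly meetings attended, and the follow-up is fixed as: "Significant MANCOVA will be followed up with both univariate tests and discriminant function analyses (DFA) to understand significant effects". The purpose given for DFA is that "DFA can be used to identify variates (combinations of dependent variables) and how the dependent variables contribute to the variates".

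No grouping factor other than occasion is named, and meetings attended is a covariate. Section 5.8.2 does not say that the DFA is to be run on change scores or with a within-woman covariance.

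**The concern.** DFA finds the combination of outcomes that best separates distinct groups, relative to the spread of scores within those groups. Here the groups are two occasions in the same women. The spread within an occasion includes lasting differences between women, which carry no information about change but still enter the weights. Making the mean comparisons paired elsewhere in the analysis leaves these weights as they are.

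What is at stake is the reading of a significant result. Research Question 2 asks whether each outcome differs before and after the intervention. If the weights are read as each outcome's share in the change, they answer a different question, and their signs and ranking may partly follow from how women differ from one another.

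**Working it through.** **Stated figure.** The protocol gives no number for the DFA. The nearest is the sample size: "There are 7 outcome variables, and a minimum sample size of 20 participants per variable is recommended for MANOVA", with the statement that "160 would be the minimum sample size required to detect a significant effect". 7 × 20 = 140, not 160; 8 × 20 = 160 matches the eight scores listed in Sections 5.8.1 and 5.8.2; 160 / 0.80 = 200 gives the recruitment target. That mismatch is a separate matter. Here 160 serves only as the simulated sample size.

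**Inputs.** From the protocol: one cohort, two linked occasions, time as the tested factor, four outcomes in one set. Not in the protocol, so assumed: SD 1; pre/post correlation (ICC) 0.3 to 0.7, equal for all outcomes; correlation of the stable parts (r_B) 0 to 0.7; correlation of the within-woman parts (r_E, which is also the correlation of change scores) 0 to 0.5; gains of 0.2 to 0.6 SD.

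**Formulas.** Let d be the vector of mean changes, B the stable between-woman covariance and E the within-woman covariance.

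- Ordinary two-group DFA: weights ∝ S⁻¹d, with S = B + E.
- Change scores: weights ∝ (2E)⁻¹d, because B cancels in the difference. Change scores form one group, so this is not an ordinary DFA.
- Two outcomes with SD 1 and correlation r: w₁ ∝ d₁ − r·d₂ and w₂ ∝ d₂ − r·d₁. So w₂ < 0 when r > d₂/d₁. This holds for both methods; only r differs. DFA uses r = ICC·r_B + (1 − ICC)·r_E, and change scores use r = r_E.

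**Two outcomes, gains 0.6 and 0.2 SD.** The sign turns at r = 0.2/0.6 = 0.33. First row: r = 0.7 × 0.7 + 0.3 × 0 = 0.49; w₁ ∝ 0.6 − 0.098 = 0.502; w₂ ∝ 0.2 − 0.294 = −0.094; ratio −0.19.

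| ICC | r_B | r_E | r in DFA | w₂/w₁, DFA | w₂/w₁, change scores |
|---|---|---|---|---|---|
| 0.7 | 0.7 | 0 | 0.49 | −0.19 | +0.33 |
| 0.7 | 0.7 | 0.2 | 0.55 | −0.27 | +0.14 |
| 0.5 | 0.3 | 0.2 | 0.25 | +0.09 | +0.14 |
| 0.7 | 0.5 | 0.5 | 0.50 | −0.20 | −0.20 |
| 0.7 | 0.3 | 0.5 | 0.36 | −0.03 | −0.20 |

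**Four outcomes, gains 0.6, 0.4, 0.2, 0.2 SD** (n = 160, 2,000 simulated trials). The last column is the share of trials in which a given 0.2 SD outcome got a negative weight. Only ratios within a set of weights matter.

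| ICC | r_B | r_E | Population weights, DFA | Population weights, change scores | Negative: DFA / change scores |
|---|---|---|---|---|---|
| 0.7 | 0.7 | 0 | 0.63, 0.24, −0.15, −0.15 | 1.00, 0.67, 0.33, 0.33 | about 90% / 1% |
| 0.5 | 0.7 | 0 | 0.56, 0.25, −0.06, −0.06 | 0.60, 0.40, 0.20, 0.20 | about 67% / 2% |
| 0.5 | 0.3 | 0.3 | 0.54, 0.26, −0.03, −0.03 | 0.54, 0.26, −0.03, −0.03 | about 60% / 60% |
| 0.7 | 0 | 0.3 | 0.55, 0.33, 0.11, 0.11 | 0.90, 0.43, −0.05, −0.05 | 8% / 63% |

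When r_B = r_E and the ICC is the same for every outcome, B is proportional to E, the two sets of weights are proportional, and the distortion of the weights vanishes. Otherwise it can go either way.

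**Structure coefficients.** With w = S⁻¹d, Sw = d, so the correlation of outcome j with the variate is (dⱼ/sⱼ)/√(dᵀS⁻¹d), where sⱼ is its SD. This keeps the sign of the mean change. The sign problem therefore concerns the weights, not these correlations.

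**The case against.** The strongest case against the point has four parts.

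- **Negative weights are not a result of ignoring pairing.** They are a general property of multivariate weights with correlated outcomes. This stands: the tables show them with correct pairing, and in one setting more often than with ordinary DFA. A reader might infer that the planned DFA will report improved outcomes as negative while a paired version would not. That contrast appears only if a high correlation is assumed for one method and a low one for the other, and the protocol supports neither choice.
- **The weights do not reflect stable differences alone.** This also stands. The pooled covariance contains both parts, and at an ICC of 0.3 the within-woman part is the larger.
- **The univariate tests still address which outcomes changed.** This stands too. A reader might infer that the plan gives a wrong answer to Research Question 2. It does not follow: a weight is a contribution given the other outcomes, a negative one does not mean that the outcome worsened, and the protocol does not say whether weights or structure coefficients will be read.
- **The form of the follow-up may be left to a SAP.** The ID linkage, and the statement in Section 5.8.2 that differences in participants' scores will be compared, leave room for a within-woman analysis. This stands only in part. The protocol itself names DFA, and on change scores there is one group, so ordinary DFA cannot be run. A SAP could repair this only by replacing the named method.

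**Conclusion.** The point holds in a limited form. The follow-up named in Section 5.8.2 does not fit a single cohort measured twice: it takes paired records as independent and uses a covariance that mixes stable and within-woman variation. This follows from the design and needs no assumed figure.

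The size and direction of the effect on the weights cannot be determined from the protocol. The figures above rest wholly on assumed SDs, gains and correlations, and they range from a strong distortion through none to one in the opposite direction. They show that the weights depend on quantities unrelated to change. They do not predict what this trial would report. Weights of this kind, paired or not, should not be read as showing which outcomes changed.

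Severity is minor: DFA is an explanatory step taken after a significant MANCOVA, it is not the main test, and the univariate tests are planned beside it.

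**What to change.** In Section 5.8.2, delete DFA as a follow-up. State that which outcomes changed is judged from each outcome's mean within-woman change with a 95% CI, from a paired univariate analysis. If a multivariate combination is still wanted, compute it from the change scores (inverse covariance of the changes times the mean change) and label it descriptive only, since its weights can also be negative for an outcome that improved.

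The cost is a change of wording and somewhat less analysis. The ID-linked scores are already to be collected. One descriptive output is lost.
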